## Abstract

As the development of the Internet and social media has led to pervasive data collection and usage practices, consumers’ privacy concerns have increasingly grown stronger. While previous research has investigated consumer valuation of personal data and privacy, only few studies have investigated valuation of different privacy aspects (e.g., third party sharing). Addressing this research gap in the literature, the present study explores Internet users’ valuations of three different privacy aspects on a social networking service (i.e., Facebook), which are commonly captured in privacy policies (i.e., data collection, data control, and third party sharing). A total of 350 participants will be recruited for an experimental online study. The experimental design will consecutively contrast a conventional, free-of-charge version of Facebook with four hypothetical, privacy-enhanced premium versions of the same service. The privacy-enhanced premium versions will offer (1) restricted data collection on side of the company; (2) enhanced data control for users; and (3) no third party sharing, respectively. A fourth premium version offers full protection of all three privacy aspects. Participants’ valuation of the privacy aspects captured in the premium versions will be quantified measuring willingness-to-pay. Additionally, a psychological test battery will be employed to examine the psychological mechanisms (e.g., privacy concerns, trust, and risk perceptions) underlying the valuation of privacy. Overall, this study will offer insights into valuation of different privacy aspects, thus providing valuable suggestions for economically sustainable privacy enhancements and alternative business models that are beneficial to consumers, businesses, practitioners, and policymakers, alike.

## Introduction

The advent of the Internet and social media has drastically transformed all aspects of our lives; how we work, consume, and communicate (see also Stewart and Segars, 2002; Paine et al., 2007). While this has had considerable advantages for society overall, the growing influence of the Internet and technologies has always been linked to concerns for privacy and the collection and use of personal information (e.g., Zuboff, 1988). The threats to individual privacy through these technologies have been repeatedly documented. Over the past years, sensitive personal data were repeatedly unlawfully obtained and mishandled in numerous data breaches. Most recently, sensitive personal information, including credit scores, of almost 150 million people was compromised in the 2017 Equifax data breach (e.g., Zou and Schaub, 2018) and around 87 million Facebook users were impacted by the Cambridge Analytica data scandal in 2018 (e.g., Revell, 2018).

While some consumers are unaware of the data they produce or of the full extent to which their data are mined and analyzed (e.g., Turow et al., 2005), others do not care (Garg et al., 2014). A majority of consumers, however, report concerns about their online privacy (e.g., Phelps et al., 2000; Pew Research Center, 2014), and, yet, most people often trade their personal data for online services and products (Carrascal et al., 2013). For instance, even privacy-concerned individuals join social networking services, such as Facebook, and share large amounts of personal information on these platforms (Acquisti and Gross, 2006).

Several factors play a role in explaining the discrepancy between people’s concerns and their online sharing behaviors, such as bounded rationality, cognitive biases and heuristics, or social factors (see Kokolakis, 2017 for a review). One explanation is the so-called privacy calculus, which postulates that people perform a calculus of the costs (i.e., loss of privacy) and benefits (i.e., gain from information disclosure). Their final decisions and behaviors are a result of this calculus and determined by the outcome of this trade-off. When the perceived benefits outweigh the perceived costs, people are likely to disclose information (Culnan and Armstrong, 1999; Dinev and Hart, 2006b). Other factors accounting for this discrepancy are, for instance, that privacy functionalities are often not usable leaving users with little choice or alternatives and making it almost impossible for users to act upon their concerns (Iachello and Hong, 2007; Lipford et al., 2008). Experts call for better data and privacy regulations as well as alternative business models to balance the asymmetric relationship between consumers and business (e.g., Zuckerman, 2014; Tufekci, 2015; Gasser, 2016; New York Times, 2018; Quito, 2018). Understanding Internet users’ privacy concerns and valuations is essential to develop strategies that match users’ needs and enable them to act in accordance to their concerns.

The present research investigates Internet users’ concerns and valuation of privacy in the context of the social networking service Facebook. In the experimental online study, participants will be presented premium versions of Facebook that offer different privacy enhancements (e.g., less data collection, more data control, and no third party sharing) for a monthly fee. Participants will be asked to indicate their willingness-to-pay for these privacy enhancements. In addition, psychological mechanisms underlying these valuations will be examined. In the following, the scientific literature underlying this research will be reviewed and the research hypotheses for this research will be developed. The experimental design and research methods will be outlined and the anticipated results presented and discussed.

## Theoretical Background

Privacy concerns have become one of the most central themes in the digital era, likewise for scholars, consumers, businesses, practitioners, and policy-makers. Acquisti and Gross (2009), for example, demonstrated the threat to individual privacy by inferring identities (i.e., social security numbers) through supposedly “anonymized” data. Other research showed that sensitive personal information, such as sexual orientation, could be inferred from Facebook Likes and facial images (Kosinski et al., 2013; Wang and Kosinski, 2018). Most recently, several data breaches, such as the Cambridge Analytica scandal that compromised personal data of about 87 million Facebook users worldwide (Revell, 2018), have sparked ethical debates on users’ online privacy (e.g., Zunger, 2018).

Although not a novel concept, there is no clear consensus on the definition of privacy (Solove, 2006). Privacy is a complex, multidimensional construct that has been studied from different perspectives (Laufer and Wolfe, 1977) and, accordingly, has been operationalized in many different ways (e.g., as an attitude in Buchanan et al., 2007; as a value in Earp et al., 2005; Alashoor et al., 2015; as a behavior in Jensen et al., 2005; or as a right in McCloskey, 1980; Warren and Brandeis, 1890; see also Bélanger and Crossler, 2011 for a review). In order to tackle privacy in a standardized and reliable manner, most contemporary research concerned with online privacy uses the construct of privacy concerns as a proxy to explore information privacy (see Dinev et al., 2009; Smith et al., 2011). Hence, a control-centered definition of information privacy prevails, where privacy is defined as individual ability to control disclosure and use of personal information (Westin, 1968; Altman et al., 1974; Margulis, 1977). Accordingly, privacy concerns can be defined as consumers’ perceptions of how the information they provide online will be used (Dinev and Hart, 2006a), and if this use can be regarded as ‘fair’ (Malhotra et al., 2004). Two widely accepted models of privacy exist that treat privacy concern as a multidimensional construct: The multidimensional instrument developed by Smith et al. (1996) assesses “individuals’ concerns about organizational information privacy practices” (p. 167). This instrument has been adapted by Malhotra et al. (2004), making it applicable to the context of online privacy. The Internet User’s Information Privacy Concerns (IUIPC) model consists of three dimensions, namely collection, control, and awareness. The dimension collection refers to users’ concerns regarding the collection of their personal information. The dimension control refers to users’ beliefs to have the right to determine and control how their information are collected, stored, and shared. The dimension awareness refers to users’ awareness of data privacy practices of companies (i.e., online service providers).

Despite the importance of privacy in the digital era, people – paradoxically even those holding strong privacy concerns – often trade their personal data for online services and products (Carrascal et al., 2013). For example, Acquisti and Gross (2006) demonstrated that even privacy-concerned individuals join the social networking service Facebook disregarding its privacy policies and revealing large amounts of personal information. The term “privacy paradox” has been coined to describe this dichotomy between expressed privacy concerns and actual online disclosure and sharing behaviors (Norberg et al., 2007). This paradox is particularly pronounced on social networking platforms, given the seemingly contradictory relationship between information privacy and social networking (i.e., connecting and sharing personal information with an online network; Lipford et al., 2012).

Many researchers have attempted to unravel and explain the privacy paradox (e.g., Barnes, 2006; Pötzsch, 2008; Sundar et al., 2013; Motiwalla and Li, 2016). One explanation defines the privacy paradox in terms of trade-offs between the benefits of using digital products and services and disclosing information online at the cost of a (partial) loss of privacy. These cost-benefit analyses are modeled as privacy calculus (Culnan and Armstrong, 1999), where privacy and personal information are conceptualized in economic terms as commodities (Klopfer and Rubenstein, 1977; Bennett et al., 1995). Willingness-to-pay is a commonly used indicator to quantify consumers’ economic valuation of commodities, such as goods and services (e.g., Casidy and Wymer, 2016; Lee and Heo, 2016). Accordingly, many scholars use willingness-to-pay as an indicator for economic valuations of privacy and information disclosure (e.g., Grossklags and Acquisti, 2007; Beresford et al., 2012; Spiekermann et al., 2012; Acquisti et al., 2013; Schreiner and Hess, 2015). Tsai et al. (2011) demonstrated that, when sufficient privacy information is available, people are willing to pay a premium to be able to purchase from websites that offer greater privacy protection. Studying low-priced products, the authors found that people were willing to pay up to 4% – around US$0.60 – more for enhanced privacy. Egelman et al. (2009) showed that people are willing to pay up to US$0.75 for increased privacy when online shopping, particularly when shopping for privacy-sensitive items. Similarly, a quarter of smartphone users were willing to pay a US$1.50 premium to use a mobile app that made fewer requests to access users’ personal information (Egelman et al., 2013). In a study by Hann et al. (2007) among U.S. Americans, personal information was worth US$30.49 – US$44.62. In another study, participants expressed high sensitivity to and concern for privacy, but only half of the participants were actually willing to pay for a change in data protection laws that would give them property rights to their personal data. The economic value placed on these privacy rights averaged around US$38 (Rose, 2005). Schreiner et al. (2013) tested privacy-enhanced premium versions of Facebook and Google and measured consumers’ propensity to pay for these services. The authors found that the optimal price for Facebook was aaa1.67/month and the optimal price for Google’s search engine lay between aaa1.00 and aaa1.50/month. Even though participants in the study were willing to pay for privacy-enhanced premium version, these valuations are relatively low (see also Bauer et al., 2012). Different explanations can account for the rather low valuations of privacy and data protection. For example, individuals who have not experienced invasion of their information privacy (e.g., through breaches or hacks) do not understand all the possible consequences resulting from information privacy violations and, therefore, tend to undervalue privacy (Hann et al., 2002). It might also be because many costs associated with the invasion of privacy occur from secondary use of information (Laudon, 1996), of which the consequences are often only experienced ex post (Acquisti, 2004). What is more, not all the costs of unprotected personal information are easy to quantify – while some of the consequences are tangible (e.g., identity theft), others are intangible (e.g., revealing personal life history to strangers; Brandimarte et al., 2015). Hence, it seems likely that people value privacy aspects that are tangible and immediate more than others.

In addition to these factors, several psychological characteristics have been identified in explaining consumers’ concerns and valuation of privacy. A large body of the literature shows that cognitive biases and heuristics, such as comparative optimism, overconfidence, or affect bias play an important role (see Kokolakis, 2017 for a review). For example, low privacy valuations are associated with people’s underestimation of one’s own and overestimation of other’s likelihood of experiencing misuse of personal data (Syverson, 2003; Baek et al., 2014), which could translate into low privacy valuations. Valuation of online privacy has also been linked to perceptions of usefulness, risk, and trust toward companies or services (e.g., Malhotra et al., 2004; Milne and Culnan, 2004; Dinev and Hart, 2006a; Garg et al., 2014; Schreiner and Hess, 2015). Prior context-specific disclosure behaviors are additional indicators of consumers’ valuations (Motiwalla et al., 2014). Therefore, it seems that the willingness-to-pay for online privacy is a telling measure, but only if considered in light of its psychological drivers.

While there is no shortage of willingness-to-pay studies trying to quantify the valuation of privacy (see also Acquisti et al., 2013), only very few studies have investigated the perception or valuation of different aspects of privacy. Hann et al. (2002) used conjoint analysis to examine the importance people ascribe to the different privacy concern dimensions of Smith et al. (1996), showing that websites’ secondary use of personal information is perceived as most important, followed by improper access of personal information. An earlier study using consumer ratings yielded similar results showing that consumers were more concerned about improper access and unauthorized secondary use than about data collection and possible errors in their data (Esrock and Ferre, 1999). Another conjoint analysis identified consumer segments based on their differing levels of privacy concerns, highlighting the need for different premium accounts that cater to consumers’ differing privacy preferences (Krasnova et al., 2009).

To our knowledge, no study has so far investigated whether these patterns can be replicated for Malhotra et al.’s (2004) adapted model of privacy concerns and no study has investigated consumers’ valuation of these privacy aspects in the context of social networking services. For example, a study by Schreiner et al. (2013) examined social media users’ willingness-to-pay for information privacy on Facebook, but did not differentiate between the three dimensions of privacy and, therefore, does not provide insights into which aspects of privacy are most valued by users. Additionally, the study by Schreiner and colleagues was limited in that they excluded non-members of Facebook, which constitutes an interesting consumer segment when it comes to privacy-enhanced premium versions of social networking services, as this segment may be especially interested in joining privacy-enhanced versions of such platforms.

## Study Objectives and Research Hypotheses

Filling these research gaps, the overarching objectives of the present study are twofold: first, the study will explore users’ valuation of three different privacy aspects in the context of social networking services and, second, the study will investigate the psychological mechanisms underlying users’ overall valuation of privacy.

Investigating the former, three privacy aspects will be studied that are captured in Facebook’s Data Policy (Facebook Inc., 2016) as well as in Malhotra et al.’s (2004) multidimensional model of privacy. These three privacy aspects are (1) data collection, (2) data control, and (3) third party use. Accordingly, participants will be offered enhancement of these three privacy aspects within hypothetical premium versions of Facebook. Precisely, these privacy-enhanced premium versions of Facebook will offer (1) restricted data collection on side of the company, (2) enhanced data control for users, and (3) no sharing of users’ data with third parties. Willingness-to-pay for the premium versions will be used as a proxy for participants’ valuation of these privacy aspects. Expanding on previous studies (e.g., Schreiner et al., 2013), this study’s insights will provide a more detailed understanding of users’ valuation of different aspects of privacy. It is explored whether Internet users value some aspects of privacy more than others. Though previous research suggests that third-party sharing may be valued most (Esrock and Ferre, 1999; Hann et al., 2002), we argue that it is also possible that companies’ restrictions on data collection may be valued more, since if no data are collected, users may be less worried about their data being shared with third parties. At the same time, the prevailing control-centered definition of privacy may invoke stronger valuations of the data control aspect. In light of these contradictory assumptions, for the present research no directional hypotheses can be formulated for the valuation of the three privacy aspects.

Investigating the latter, that is, the psychological mechanisms underlying valuation of privacy on social networking services, the present study will test a theoretical model that is developed and adapted based on proposed models by Malhotra et al. (2004) and Wilson and Valacich (2012). These models propose that privacy concerns increase perceived risk of information disclosure online and, thus, influence people’s intentions to protect their data. This relationship is expected to be further moderated by several other psychological and socio-demographic characteristics measured in this study. It is hypothesized that the proposed model will explain the psychological mechanisms underlying valuation of privacy on Facebook (see Section Theoretical Model).

## Materials and Methods

### Participants

We aim to recruit at least 350 English-speaking adults (i.e., minimum age of 18 years). The estimated sample size is based on Lipovetsky’s (2006) estimation that a minimum of 256 participants are needed to set up a price model with the precision of 𝜀 = 0.05 and to reach value close to 80%. Taking into account potential dropouts and invalid participant responses, we aim to reach sample size of a minimum of 350 participants. Though participant recruitment is restricted to English-speaking adults, we will, unlike previous studies (e.g., Schreiner et al., 2013), recruit participants across different countries^1^. As statistics report differing levels of privacy concerns and social media use across countries and cultures (e.g., Eurobarometer, 2016), we hope that our recruitment strategy will enable us to capture a heterogeneous participant sample with respect to the level of concern for and valuation of privacy. Furthermore, we will include both Facebook members and non-members in the sample. Facebook non-members are an important subsample, as this consumer segment could have a particular interest in privacy-enhanced versions of social networking services like Facebook. To ensure these sampling criteria, we will make use of various online channels, such as social networks and specialized study recruitment pages (e.g., findparticipants.com), as well as mailing lists, university platforms, and topic-relevant online forums.

### Experimental Design

In the present online study, we will create four hypothetical privacy-enhanced premium versions of Facebook. The privacy enhancements of the premium versions will be based on three privacy aspects that are captured both in the IUIPC model (Malhotra et al., 2004) as well as in Facebook’s Data Policy (Facebook Inc., 2016). Three of these premium versions will have one specific privacy aspect enhanced: in the first condition, data collection policies will be less permissible, thus, granting users the option that Facebook collects less data about them; the second condition will offer enhanced data control for users and allows complete or selective deletion of stored data; in the third condition, users will have the option to opt out from having Facebook share their data with third parties, such as advertisers (see **Figures 1**–**3**). An additional fourth condition will consist all three privacy enhancements in a full-design premium version.

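### Experimental Design words version 3, and partly version 1, as user options, which departs from the stated objectives and partly overlaps with the data control version

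*Protocol article*

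**What the plan says.** Study Objectives and Research Hypotheses describes the first two premium versions as offering "restricted data collection on side of the company, (2) enhanced data control for users" and the third as "no sharing of users’ data with third parties". The Abstract describes them in the same way.

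Experimental Design promises one aspect per version: "Three of these premium versions will have one specific privacy aspect enhanced". It then describes the content:

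- **Version 1 (data collection):** stricter company policies on collection, with the consequence stated as "granting users the option that Facebook collects less data about them".
- **Version 2 (data control):** "the second condition will offer enhanced data control for users and allows complete or selective deletion of stored data".
- **Version 3 (third party sharing):** "in the third condition, users will have the option to opt out from having Facebook share their data with third parties, such as advertisers".

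Theoretical Background describes the privacy model on which the versions are based and states: "The dimension control refers to users’ beliefs to have the right to determine and control how their information are collected, stored, and shared".

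The Willingness-to-Pay Measure section uses the single overall price item to compare the three enhancements and to conclude which is valued most. Anticipated Results names differences in valuation of the three aspects as a main aim.

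**The concern.** A restriction that the company applies to everyone who buys the product is a different good from an option given to the user. In the same way, a product that does not share data differs from one that lets the user opt out of sharing. The article describes versions 1 and 3 in one way where it sets the aims and in another where it specifies the conditions.

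The difference between the two descriptions is user choice, and user choice over collection or sharing belongs to control as the article defines it. If the stimuli follow Experimental Design, some of what version 2 is meant to isolate is also on offer in versions 1 and 3.

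Two things are at stake. The ranking of the three aspects could place control too low because of how the stimuli are worded. And a price would be reported for the absence of third party sharing when participants had priced an opt-out. The discussion in Anticipated Results intends to derive direct suggestions for privacy enhancements from this ranking.

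**Working it through.** The plan states no figure on this point, so the check is a comparison of texts, followed by a short piece of algebra for the direction.

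**Texts side by side**

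| Version | Abstract and Study Objectives | Experimental Design | User choice added? |
|---|---|---|---|
| 1, collection | Restriction on the company's side | Stricter company policy, which gives users an option for less collection | Partly |
| 2, control | Enhanced control for users | Enhanced control; the concrete feature named is deletion of stored data | Intended |
| 3, sharing | No sharing with third parties | User may opt out of sharing | Yes |

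The two descriptions differ clearly for version 3 and in part for version 1.

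**Link to control.** The definition in Theoretical Background names three objects of control: collection, storage and sharing. An option over collection falls under the first and an opt-out from sharing under the third. Deletion in version 2 falls under the second. So all three versions, as Experimental Design words them, contain some control, although each acts on a different object.

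**Rationale.** Study Objectives argues that restricted collection might be valued most because data that are never collected cannot cause worry about sharing. It sets this against a control-centred view that would favour version 2. That contrast needs version 1 to be actual non-collection and not a choice about it.

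**Direction.** Assume additive values: *a* for restricted collection, *c* for control, *s* for no sharing. Let *k1* and *k3* be the unknown fractions of *c* carried by versions 1 and 3, each between 0 and 1, with *a* and *s* otherwise unchanged.

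- Control versus sharing: intended *c − s*; obtained *c − (s + k3·c) = (1 − k3)·c − s*; shift *−k3·c*.
- Control versus collection: intended *c − a*; obtained *c − (a + k1·c) = (1 − k1)·c − a*; shift *−k1·c*.
- Collection versus sharing: intended *a − s*; obtained *(a − s) + (k1 − k3)·c*; shift of either sign, zero if *k1 = k3*.

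For any positive *k* and *c*, both contrasts that involve version 2 move against control. At *k* = 0 there is no shift, and at *k* = 1 the whole of *c* drops out. The documents give nothing that narrows this range.

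**Safeguards in the plan.** Stepwise Procedures randomises the order of the three versions, which deals with order effects. Its control questions check that participants understood the enhancements. Neither removes an overlap that lies in the content of the versions.

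**The case against.** The strongest reply is that Experimental Design is only a summary. Participants see adapted policy text as bullet points, shown in Figures 1 to 3, and those figures are not visible here. The bullets may already say without condition that data are not shared. This stands: that participants priced an opt-out is conditional on the stimuli following the summary. If they do not, Experimental Design misdescribes them and still needs correcting.

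Second, the clause on version 1 begins with a change in company policy and presents the option as its consequence. That fits the objectives better than the option phrase alone suggests, so version 1 departs only in part.

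Third, the option could be read as the choice to buy the premium version, with no setting for the user to manage. This is possible for version 1. It is harder to hold for version 3, where opting out is named as the feature itself.

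Fourth, the definition of control comes from an attitude scale and not from a specification of stimuli. The article also notes that privacy as a whole is commonly defined through control. Some overlap may therefore remain after any rewording. That limits what the fix can achieve but does not justify adding choice to versions that are meant to isolate something else.

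A reader might go further and infer that the three versions fail to separate the aspects at all, or that versions 1 and 3 simply are the data control version. The documents do not support this. Version 2's concrete feature is deletion of stored data, the versions act on different objects, and a ranking among them would still carry information. Nor do the documents support any particular share of the control value being lost.

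**Conclusion.** The point holds as an inconsistency with a likely consequence. Experimental Design and the objectives describe different goods for version 3, and in part for version 1. If the stimuli follow Experimental Design, versions 1 and 3 partly overlap with data control, and differences among the three within-subject conditions cannot be attributed cleanly to one aspect.

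The expected direction is against control. This assumes additive values, a positive value for user choice, and no other change in what versions 1 and 3 are worth. The size is unknown: it depends on the stimulus wording and on a fraction for which the documents give no basis. The structural equation model uses the full-design version, which combines all three enhancements, so the ranking problem does not carry over to it directly.

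**What to change.** Before launch, reconcile Experimental Design with the Abstract and Study Objectives, and check the texts behind Figures 1 to 3 against them. Word version 1 as a restriction that the company applies and version 3 as no sharing with third parties, with no user setting in either. Keep user choice and deletion in version 2 only. Carry the same wording into the full-design version.

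If the option wording is kept, describe the versions in the aims and conclusions as control over collection, control over stored data and control over sharing, and do not report a price for the absence of sharing.

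The cost is the rewording of a few bullet points and slightly less closeness to the original Data Policy text. Once responses have been collected, the stimuli can no longer be corrected; only the labels can.
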